### Interventions and control groups

5.3

**Full intervention group:** Participants in this group will undergo comprehensive training encompassing both technical and soft skills. The technical curriculum covers a range of software programs including Microsoft Excel, Power BI, SQL, GitHub, R, Tableau, statistics, and Python. These technical sessions will be delivered remotely in one-hour seminars, four days a week, with each software program's training lasting between 2 and 5 weeks starting September 2025. In addition to technical training, participants will also engage in soft skills development through workshops focused on empowerment, employability, and public speaking. These workshops will consist of four-hour in-person sessions held on weekends, approximately every three weeks. To culminate their learning experience, participants will be required to complete and present a capstone project.

**Training dose and supports:** Technical modules total approximately 80–120 contact hours across Excel, Power BI, SQL, GitHub, R, Tableau, statistics, and Python (1 h sessions, 4 days/week, 2–5 weeks per module), complemented by weekly office hours and pre-class micro-tasks (15–30 min). Soft-skills workshops (empowerment, employability, public speaking) total ∼24 h (in-person, weekend sessions). The capstone requires ∼30–40 h of independent/team work culminating in a public presentation with rubric-based assessment.

**Partial intervention group:** This group will receive a more focused intervention, limited to workshops on empowerment, employability, and public speaking. This targeted approach allows for the assessment of the specific impact of soft skills training on participant outcomes.

**Control group**: Comprising individuals who just miss the cut for full program admission, this group will not receive any intervention. This setup enables a clear comparison to be made between those who receive interventions and those who do not, providing insight into the program's overall effectiveness. Participants for both the partial intervention and control groups will be selected randomly from a pool of applicants who narrowly miss selection for the full intervention, ensuring no significant differences in observable characteristics among the groups.

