### Baseline, endline, and follow-up assessments

5.5

Participants will be asked to complete the questionnaires at three time points: baseline (the month of the start of the program), immediately following the completion of the *New Dimensions* program (endline), and one year after the end of the program (follow-up). This will allow us to track changes in outcomes over time and assess the long-term impact of the program on participants. Participants will receive the questionnaires electronically and be given a set amount of time to complete them. Reminders will be sent to those who have not completed the questionnaire in a timely manner. All information collected will be kept confidential and will be used only for research purposes.

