### Sample size

5.8

The sample size for this study will consist of 80 participants, including 50 in the full intervention group, 20 in the soft skills-only group, and 10 in the control group. This study is exploratory in nature due to resource constraints, particularly funding limitations and logistical challenges in delivering training sessions. The sample size was determined based on the maximum feasible recruitment capacity within the available resources rather than a formal statistical power calculation. While a larger sample would enhance the statistical power of the findings, this study serves as an initial investigation into the effectiveness of the New Dimensions program, providing preliminary evidence that can inform future large-scale studies and programs.

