### Statistical plan

6.3

Descriptive statistics will be used to summarize the demographic characteristics of the study population and examine the distribution of outcome variables. Continuous variables will be summarized as means and standard deviations or medians and interquartile ranges depending on their distribution. Categorical variables will be summarized as frequencies and percentages.

To assess the effectiveness of the *New Dimensions program*, we employ a quasi-experimental design with two intervention groups and one control group. The two intervention groups will be compared to the control group to evaluate the impact of the program on employability and well-being outcomes.

To test for differences in baseline characteristics between the intervention and control groups, we used *t*-tests for continuous variables and chi-square tests for categorical variables. To examine changes in the outcome variables over time, we plan to employ linear mixed-effects regression models. Models will include fixed effects for group (full/partial/control), time (baseline/endline/12-month), and the group × time interaction (primary estimand), with random intercepts for participants. These models will allow us to account for the within-subject correlation of repeated measurements over time and adjust for potential confounders, such as age and educational level. We will additionally adjust for city, baseline employment status, and motivation score (tertiles). This will help to control for variations in motivation that could impact outcomes, thereby reducing the risk of false positives. By adjusting for motivation, we aim to ensure that the observed effects are more likely to be attributable to the intervention itself rather than pre-existing differences between groups.

Missing data will be handled using complete case analysis when the proportion of missing data is low and assumed to be missing completely at random (MCAR). For cases where missingness is more substantial, we will implement inverse probability weighting (IPW) to adjust for potential differences between participants who remain in the study and those lost to follow-up. Descriptive comparisons between retained and lost participants will also be performed to assess systematic differences that could influence the results.

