All statistical tests will be two-sided, with a significance threshold of *p* < 0.05. Missing data will be addressed using Multiple Imputation by Chained Equations (MICE) under MAR assumptions, with sensitivity analyses including complete-case and IPW approaches. Given the exploratory sample size (*n* = 80), we will emphasize precision of estimates (95% confidence intervals) rather than sole reliance on *p*-values, and will apply small-sample robust standard errors where appropriate. All analyses will be conducted in Stata 19.0.

To prevent undisclosed flexibility in our analysis pipeline, as mentioned before, we have predefined all primary and secondary outcomes and will adhere strictly to the outlined statistical methods. Outcome-neutral conditions are established by employing validated instruments known to avoid floor or ceiling effects. Given that the study is exploratory due to funding and resource constraints, no formal power calculation was performed. Therefore, some analyses, particularly those involving subgroup comparisons (e.g., differences between full and partial intervention groups), should be considered exploratory. Assumptions for our analyses include approximate normality of continuous variables and that data are missing at random (MAR), both of which will be examined through diagnostic and sensitivity checks. Missing data will be addressed using Multiple Imputation by Chained Equations (MICE) under MAR assumptions, and effect sizes with 95% confidence intervals will be reported and compared across imputed and complete-case approaches. Robustness will be evaluated by repeating models both with and without adjustment for baseline motivation scores. Finally, to address potential selection bias from the non-random assignment of participants to the full-intervention group, we will perform propensity-score inverse probability of treatment weighting (IPTW) sensitivity analyses based on age, education, city, baseline employment status, and motivation score.

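### The random-intercept-only model for the group × time estimand can misstate the 95% intervals of the continuous outcomes (too wide at endline, too narrow at 12 months) if correlation falls with time, and the robust errors that could repair this are optional.

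*Protocol article*

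**What the plan says.** The Statistical plan (6.3) models outcome change with fixed effects for group, time and their interaction, the last named as the primary estimand, "with random intercepts for participants". It names no random slope and no residual covariance structure. The same section makes 95% confidence intervals the main output. It adds that the team "will apply small-sample robust standard errors where appropriate", without naming the correction, the degrees of freedom or the condition that triggers them. The model checks it lists concern normality and the missing-at-random assumption, not the covariance structure. It also commits the team to keep strictly to the methods described.

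The assessments (5.5) are at "baseline (the month of the start of the program), immediately following the completion" of the program, and "one year after the end of the program (follow-up"). The arms (5.8) are unequal: "including 50 in the full intervention group, 20 in the soft skills-only group, and 10 in the control group".

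**The concern.** A random intercept as the only within-person term forces the variance to be equal at all three visits and the correlation to be equal for all three visit pairs. The visits are unevenly spaced, and income and similar measures may well correlate less over the longest gap than over the shortest.

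The model then estimates one residual variance, averaged over the three pairs, and uses it for every change contrast. The change over the most highly correlated pair gets too large a standard error, and the change over the least correlated pair gets too small a one. The too-narrow interval would be the one at 12 months, which carries the secondary objective on sustainability of impact (4.2). Because the plan puts its weight on intervals rather than p-values, their coverage matters even in an exploratory study.

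**Working it through.** **Inputs from the document.** Arms 50/20/10; three visits; two-sided 0.05. The technical training (5.3) is 80–120 contact hours in "1 h sessions, 4 days/week, 2–5 weeks per module", across eight modules.

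**Visit spacing.**
- By hours: 80/4 = 20 weeks to 120/4 = 30 weeks.
- By modules: 8 × 2 = 16 weeks to 8 × 5 = 40 weeks.
- Baseline to endline is therefore 16 to 40 weeks, about 4 to 9 months. Endline to follow-up is 12 months. Baseline to follow-up is about 16 to 21 months.

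**Assumed.** Between-visit correlations are not in the document, so a range is used. Outcomes are normal, data complete, variances equal and the true effect zero. The document states no standard error or power figure to reproduce.

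**Formula.** For a pair of visits with correlation r, the true variance of a change is 2σ²(1 − r). The random-intercept model uses 2σ²(1 − r̄), where r̄ is the mean of the three correlations. The arm-size factor (1/50 + 1/10 for full versus control) cancels, so:

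model SE / true SE = √[(1 − r̄)/(1 − r)], and type I error = 2[1 − Φ(1.96 × ratio)].

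Example, 0.7/0.4/0.6: r̄ = 1.7/3 = 0.567.
- Endline: √(0.433/0.3) = 1.20; 1.96 × 1.20 = 2.36; type I error 1.9%.
- 12 months: √(0.433/0.6) = 0.85; 1.96 × 0.85 = 1.67; type I error 9.6%.

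Correlations below are in the order baseline–endline, baseline–12 months, endline–12 months. Simulated values come from 20,000 null trials per pattern; the reference is normal, or t on 154 df for the rows marked *.

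| Correlations | SE ratio, endline | Type I error, endline: formula (simulated) | SE ratio, 12 months | Type I error, 12 months: formula (simulated) |
|---|---|---|---|---|
| 0.5/0.5/0.5 (no decay) | 1.00 | 5.0% (5.4%) | 1.00 | 5.0% (5.3%) |
| 0.6/0.45/0.55 | 1.08 | 3.4% (3.6%) | 0.92 | 7.1% (7.4%) |
| 0.7/0.5/0.6* | 1.15 | 2.4% (2.5%) | 0.89 | 8.0% (7.8%) |
| 0.7/0.4/0.5* | 1.25 | 1.5% (1.6%) | 0.88 | 8.4% (8.3%) |
| 0.7/0.4/0.6 | 1.20 | 1.9% (1.8%) | 0.85 | 9.6% (9.8%) |
| 0.8/0.5/0.6* | 1.35 | 0.8% (0.9%) | 0.86 | 9.3% (9.2%) |

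A steeper pattern, 0.8/0.3/0.6, gives 0.5% and 12.5% by simulation.

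**What this does to the interval.** For 0.7/0.4/0.6, the true 12-month SE in SD units is √[2 × 0.6 × (1/50 + 1/10)] = 0.379, a half-width of 1.96 × 0.379 = 0.74 SD. The model reports √(2 × 0.433 × 0.12) = 0.322, a half-width of 0.63 SD. The nominal 95% interval covers about 90%.

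**Alternatives, same simulations.**
- Unstructured covariance, t on 77 df: 4.8–5.2% at both visits under equal variances.
- CR2 robust errors with Satterthwaite df (about 14): 5.0–5.4%.
- Plain cluster sandwich with only an N/(N − 1) factor and a normal reference: 7.8–8.3%, because 10 controls carry much of the variance.

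**Unequal variances by arm.** If SD grows only in the trained arms (full 1/1.3/1.6, partial 1/1.15/1.3, control 1/1/1), the random-intercept model gives 0.5% at endline and 5.1% at 12 months. The pooled unstructured model gives 2.9% and 2.0%, and CR2 with Satterthwaite gives 5.5% and 5.6%.

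**The case against.** The strongest reply is that the plan already contains the repair. It specifies small-sample robust errors, and a proper version holds the level near 5% with 10 controls even when the working covariance is wrong. The exact correction and degrees of freedom are details that a condensed article may leave to a fuller document. This stands. A reader might infer that the planned robust errors would themselves give intervals that are too narrow, but the 8% figure belongs to an uncorrected sandwich with a normal reference, which the text does not plan. What remains is that their use is discretionary and not tied to the primary model.

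Second, the correlations are assumed. Without decay the random-intercept standard error is right. When variance grows only in the trained arms, the 12-month error happens to be about nominal because two misspecifications offset. A reader might therefore go too far in saying that the planned intervals are wrong; the document supports only that they can be.

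Third, the unstructured model does well partly because the simulated arms shared one covariance. Its conservatism under arm-specific variance is real, which is why the robust errors belong beside it.

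Finally, the study is exploratory, has no power calculation, and its full arm is not randomised. That limits the weight of any single interval but gives no reason to accept a known source of miscalibration.

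**Conclusion.** The point holds in a limited form. The covariance is a stated choice, poorly suited to visits spaced this unevenly, and no listed check would reveal a misfit. If correlation decays within the range shown, 12-month intervals for the continuous outcomes are too narrow (type I error about 7 to 10%) and endline intervals too wide (about 1 to 3.6%). With no decay the level is about 5%.

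This rests on assumed correlations, equal variances across visits and arms, complete data, no covariates and the model-based standard error. It does not cover employment status, which is categorical, or the effect of imputation or weighting.

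**What to change.** For the continuous outcomes only, replace the random-intercept-only specification with a REML fit using an unstructured 3×3 within-person covariance and Kenward-Roger or Satterthwaite degrees of freedom. Always report beside it bias-reduced (CR2-type) robust standard errors with Satterthwaite degrees of freedom. Name that estimator in place of the discretionary wording, so that intervals are also guarded against variances that differ by arm.

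The cost is small: one change of model option, six covariance parameters in place of two with 80 women, and a second set of intervals to report. The downside is some conservatism of the pooled unstructured model (about 2 to 3% in the scenario above) if variance grows only in the trained arms. No extra data are needed.

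### Adjusting for motivation as a main effect leaves the group × time primary estimand unchanged in a complete or imputed panel, so the stated confounding control and the with/without-motivation check do not do what is claimed

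*Protocol article*

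**What the plan says.** Section 6.3 (Statistical plan) specifies linear mixed-effects models with fixed effects for group, for "time (baseline/endline/12-month), and the group × time interaction (primary estimand), with random intercepts for participants". Baseline is therefore one of the outcome rows, and the effect of interest is the difference between groups in change from baseline.

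The models are also to "adjust for potential confounders, such as age and educational level", and the section continues: "We will additionally adjust for city, baseline employment status, and motivation score (tertiles"). All of these are recorded once per participant. The only interaction written out is group × time.

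Two benefits are claimed for the motivation adjustment: "This will help to control for variations in motivation that could impact outcomes, thereby reducing the risk of false positives", and "By adjusting for motivation, we aim to ensure that the observed effects are more likely to be attributable to the intervention itself".

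The same section adds a check: "Robustness will be evaluated by repeating models both with and without adjustment for baseline motivation scores". Separately, it plans an IPTW sensitivity analysis for the non-random full-intervention group, using age, education, city, baseline employment status and motivation score. Section 5.10 states that the full group is chosen on economic need, academic merit and motivation, while the partial and control groups are drawn at random from near-miss applicants.

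**The concern.** A covariate that does not vary within a person shifts that person's level at every visit by the same amount. The primary estimand is a contrast of changes, from which any constant shift drops out. Main-effect adjustment therefore alters the group (level) coefficient and leaves the coefficient that answers the study question where it was.

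Two consequences follow. First, the plan credits its primary model with a protection it lacks. Group × time already removes stable level differences between groups. The remaining threat is that more motivated women, or women differing on another selection factor, would have followed a different path in employment or income anyway. Because the full arm is selected partly on motivation, this threat falls on full versus control and full versus partial. Partial versus control is protected by the random draw. Second, the with/without-motivation comparison would be reported as evidence of robustness although its agreement is arithmetically guaranteed.

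**Working it through.** The plan gives no effect size or power figure on this point, so there is none to reproduce.

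**Inputs from the article.** Groups of 50/20/10 (section 5.8). Three visits, linear model, random intercept, two-sided 0.05 (section 6.3).

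**Step 1: algebra.** Write the model for person *i* at visit *t* as

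y_it = μ_t + γ_g(i),t + βx_i + b_i + e_it,

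where x_i is motivation (or age, city and so on) and b_i is the random intercept. Then

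y_i,12m − y_i,base = (μ_12m − μ_base) + (γ_g,12m − γ_g,base) + (e_i,12m − e_i,base).

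Both βx_i and b_i cancel. With everyone seen at all three visits, the generalised least squares estimate of the 12-month interaction is

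(mean change, full) − (mean change, control),

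whatever the value of β. If the true model contains a term λx_i after baseline only, this estimate is biased by λ × (mean x in full − mean x in control), with or without βx_i in the fit.

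**Step 2: simulation with complete data.** 150 simulated trials of 50/20/10 with a true effect of 0. Assumed, not from the documents: motivation tertiles (coded 0, 1, 2) split 10/30/60% in the full arm and 40/40/20% elsewhere, and a post-baseline gain of 0.5 residual SD per tertile. Expected bias = 0.5 × [(0.3×1 + 0.6×2) − (0.4×1 + 0.2×2)] = 0.5 × (1.5 − 0.8) = 0.35.

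| Model | Mean full-vs-control 12-month interaction | Mean SE |
|---|---|---|
| No covariates | 0.335 | 0.498 |
| Main effects, motivation left out | 0.335 | 0.498 |
| Main effects, motivation included | 0.335 | 0.498 |
| Motivation × time added | −0.005 | 0.523 |
| All covariates × time | 0.002 | 0.537 |

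The first three rows agree trial by trial; the largest difference was 7e-14.

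**Step 3: the missing-data methods named in section 6.3.** In one simulated data set with about 30% missed visits, the three main-effect versions were identical under each method:

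- complete-case participants: 0.156162
- complete cases with participant-level weights: 0.500863
- pooled over 20 imputations: 0.483044

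For imputation this supposes that the same imputed data sets feed both fits.

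**Step 4: where exact invariance fails.** In an available-case mixed model on an unbalanced panel, adding all main effects moved the estimate by a mean absolute 0.04 (maximum 0.30) at about 20% missed visits, and 0.08 (maximum 0.43) at about 40%. The bias stayed: means of 0.328 and 0.314 with main effects, against 0.007 and 0.016 with motivation × time.

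**Step 5: possible size.** Bias in outcome SD = (motivation gap in SD) × (later gain per SD of motivation). Neither factor is in the documents. If the change score has SD 1 (visit-to-visit correlation 0.5), the full-vs-control SE is √(1/50 + 1/10) = 0.346. The true two-sided size is Φ(−1.96 + bias/SE) + Φ(−1.96 − bias/SE).

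| Gap (SD) | Gain per SD | Bias (SD) | Size of a nominal 5% test |
|---|---|---|---|
| 0.25 | 0.3 | 0.075 | 5.5% |
| 0.5 | 0.3 | 0.15 | 7.2% |
| 1.0 | 0.3 | 0.30 | 13.9% |
| 1.0 | 0.1 | 0.10 | 6.0% |

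**Step 6: cost of the interaction term.** From step 2, 0.523/0.498 = 1.05 with motivation × time and 0.537/0.498 = 1.08 with all covariates × time. A separate simulation gave 0.363/0.352 = 1.03 for motivation × time.

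**The case against.** The strongest reply is that the plan does address selection elsewhere. The IPTW analysis includes motivation and is aimed at the non-random full arm. Weighting does change the interaction: in the step 2 scenario, weighting on motivation tertile moved the mean change-score contrast from 0.332 to −0.034. A reader might infer that the plan leaves full versus control with no protection, and the article does not support that. What stands is that IPTW is only a sensitivity analysis, and that its covariates omit baseline income and the exam and interview scores used in selection.

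The invariance also has limits. It is exact for a linear model on balanced, imputed or participant-weighted data, not for an available-case fit with dropout or for a logistic model of employment status. The article neither states nor excludes covariate × time terms, so main effects are the natural reading rather than the only one.

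A reader might further infer that selecting on economic need builds regression to the mean in income into the estimate. That needs selection on the same income measurement that serves as baseline. Section 5.5 takes baseline by questionnaire in the month the program starts, apart from the application. With correlation 0.6 between occasions, the bias in group × time was 0.167 SD when one measurement served both purposes and 0.002 when the application measurement was separate. In the separate case, ANCOVA was the biased method (−0.10).

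Finally, controls are near-misses and low-motivation applicants are screened out (section 5.2), so the motivation gap may be well below 1 SD. The study also calls itself exploratory. That excuses low precision, but not a claimed property that the model lacks.

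**Conclusion.** The point holds, and the text is wrong as written. For the declared estimand, main-effect adjustment for motivation neither reduces false positives nor makes effects more attributable to the program, and the with/without-motivation check carries no information when the panel is complete, imputed or participant-weighted. This rests only on the stated linear model and on reading the covariates as main effects.

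The size of the remaining bias is not established. It is zero if motivation does not affect trajectory, and about 0.3 SD under the largest scenario in the step 5 table. That table is illustrative and is not an estimate of the bias in this study. The finding does not show that the primary model must be replaced. With a stable gap between groups and parallel trends, group × time is unbiased and ANCOVA is not.

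**What to change.** In section 6.3, keep the present model and add motivation × time. Add other baseline covariate × time terms sparingly, since there are only 10 controls. Redefine the robustness check as the group × time estimate with and without the motivation × time term. Replace the sentences on false positives and attribution with a statement that main effects adjust levels, and that differential trends by motivation are handled by the interaction term and by IPTW.

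A longitudinal ANCOVA can be added as a sensitivity analysis. It should not displace the primary model, because change-score and ANCOVA estimates rest on different assumptions when groups are not equivalent.

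The cost is rewording, a few degrees of freedom and a standard error about 3–8% larger in the simulations. No new data are needed.

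### As section 6.3 is ordinarily read, the motivation adjustment leaves the group × time estimate unchanged when all visits are present, so the false-positive claim and the with/without-motivation check are unsupported for the primary model

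*Protocol article*

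**What the plan says.** Section 6.3 (Statistical plan) of the protocol article gives the model and names the estimand: "Models will include fixed effects for group (full/partial/control), time (baseline/endline/12-month), and the group × time interaction (primary estimand), with random intercepts for participants". The models are also meant to "adjust for potential confounders, such as age and educational level", and the text goes on: "We will additionally adjust for city, baseline employment status, and motivation score (tertiles". The only interaction named is group × time.

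Two benefits are claimed for adjusting for motivation: "thereby reducing the risk of false positives", and attribution to the program, in the words "By adjusting for motivation, we aim to ensure that the observed effects are more likely to be attributable to the intervention itself".

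The same section later adds a check: "Robustness will be evaluated by repeating models both with and without adjustment for baseline motivation scores". For the non-random full arm it plans IPTW "sensitivity analyses based on age, education, city, baseline employment status, and motivation score". On missing data it says "Missing data will be addressed using Multiple Imputation by Chained Equations (MICE) under MAR assumptions, with sensitivity analyses including complete-case and IPW approaches". An earlier paragraph of 6.3 names complete-case analysis when little is missing and IPW when more is missing.

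Section 5.10 (Assignment of interventions) says that the full arm is chosen on economic need, academic merit and motivational merit. The partial and control arms are drawn at random from the near-miss pool, within strata of city, baseline employment and motivation tertile.

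**The concern.** The primary estimand is a difference in change. All five covariates are baseline values or are treated as such. A term that raises or lowers a woman's level equally at every visit cannot explain why she changes. So if the covariates enter as main effects, the adjustment does not act on the quantity being estimated.

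This matters because motivation is one of the criteria for entry to the full arm. If more motivated women find work or raise their income faster whatever training they get, the group × time term credits that gain to the program. The report would still describe the estimate as adjusted for motivation, and the with/without comparison would appear to confirm it. The stratification factors would also bring no precision to the randomised partial-versus-control contrast in change.

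**Working it through.** The plan gives no figure on this point, so there is nothing to reproduce. Inputs from the protocol are the arm sizes 50/20/10 (5.8), three visits (5.5), and the model, covariates and missing-data methods (6.3).

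**Step 1, algebra.** Write the model as ordinarily read for woman *i* in group *g* at visit *t*:

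Y(i,t) = α + γ(g) + τ(t) + δ(g,t) + β′X(i) + u(i) + e(i,t)

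Her change from baseline to 12 months is

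Y(i,12m) − Y(i,0) = [τ(12m) − τ(0)] + [δ(g,12m) − δ(g,0)] + [e(i,12m) − e(i,0)].

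Both β′X(i) and u(i) cancel. With all visits present, the full-versus-control interaction is the difference in mean change, whatever X contains. The same holds in each imputed dataset, provided that both fits use the same imputations.

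If motivation M also adds λM(i) after baseline, the contrast becomes the true effect + λ × (mean M in full − mean M in control). A main effect of M does not remove the second part; M × time does.

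**Step 2, numerical check.** These assumptions are not from the protocol: true program effect 0; motivation coded 0, 1, 2 with probabilities 0.15/0.30/0.55 in the full arm and 0.45/0.35/0.20 in control; 5 points extra gain per tertile step after baseline; intercept and residual SD 6 each.

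Mean M is 0.30 + 2 × 0.55 = 1.40 in full and 0.35 + 2 × 0.20 = 0.75 in control. Expected bias is 5 × (1.40 − 0.75) = 3.25 points.

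In one complete dataset the 12-month interaction was 5.45771422 without covariates, with all main effects except motivation, and with all main effects (SE 3.1261 each time). Motivation × time gave 3.68 and the full set of covariate × time terms gave 6.68, so a single dataset shows the invariance but not the bias.

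Means over 200 datasets, full versus control at 12 months, true value 0 (missingness rates are nominal and apply to follow-up visits):

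| Data | No covariates | All main effects | Motivation × time added | IPTW on change |
|---|---|---|---|---|
| Complete | 3.41 | 3.41 | 0.20 | 0.72 |
| 20% of visits missing at random | 2.74 | 2.78 | −0.28 | 0.44 |
| 20% missing, depending on motivation | 2.71 | 2.85 | −0.18 | 0.36 |
| 35% missing, depending on motivation | 2.84 | 3.05 | 0.15 | 0.80 |

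The mean SE in the complete case was 3.14, so the Monte Carlo error of a mean is about 3.14/√200 = 0.22. The 3.41 agrees with the expected 3.25, and the 0.20 agrees with 0.

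**Step 3, the with/without-motivation check.** The absolute difference between the two fits was 0 in every complete dataset. With missing visits and all available rows used, it averaged 0.28, 0.36 and 0.57 in the three scenarios (largest 1.59, 1.71 and 4.05), against mean SEs of 3.43, 3.52 and 3.95. The bias remained.

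**Step 4, error rate.** A separate simulation (1,500 trials per scenario) assumed no program effect, within-woman correlation 0.5, and top-tertile motivation in 50% of the full arm against 20% of near-miss women. Extra 12-month gains of 0.5, 1.0 or 1.5 SD for top over bottom tertile gave bias of 0.15, 0.31 or 0.44 SD. Rejection was 8.5%, 12.7% or 19.7% at a nominal 5%. With covariate × time terms the bias was about 0 and rejection 5 to 6.5%.

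**Step 5, cost in parameters.** Motivation tertiles (2 terms) × 2 follow-up times = 4. City adds 1 × 2 = 2, and baseline employment adds 1 × 2 = 2. All five covariates need at least (2 + 1 + 1 + 1 + 1) × 2 = 12.

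**The case against.** **The form of entry is inferred.** The article never says main effects only, and a condensed article may leave such detail to a fuller document. This stands as a caveat. But 6.3 lists its terms, names one interaction and commits the team to the outlined methods. Main effects are the ordinary reading, and the claimed benefit is stated in the text itself.

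**A reader might infer that confounder control is absent altogether.** The document does not support that. The change contrast already removes stable level differences between groups. The planned IPTW analysis uses the same five covariates and does act on change, moving 3.41 to 0.72 in the check above. It is, however, a sensitivity analysis with 10 controls, and it does not make the claim for the primary model true.

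**A reader might infer that the estimate can never move and that the check always passes.** That is exact only for balanced or imputed data. Section 6.3 names several missing-data methods, and with unbalanced rows the two fits differ somewhat. They differ without removing the bias.

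**The sizes are assumed.** Low-motivation applicants are screened out (5.2) and controls narrowly miss admission, so the real imbalance may be smaller. The correction performs well partly because the simulated confounding is the confounding it models. Both points stand. The invariance with complete data depends on none of this.

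**The study calls itself exploratory and stresses intervals over p-values.** True, but an estimate biased by differential change has a misplaced interval too.

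**Conclusion.** The point holds for the primary model. With all three visits present, main-effect adjustment leaves the group × time estimate exactly as it was. With unbalanced data it moves the estimate by little on average (0.28 to 0.57 points against SEs of 3.4 to 4.0) and does not remove confounding of change. The statements that adjusting for motivation lowers false positives and supports attribution are therefore unsupported for that model, and the with/without-motivation comparison is uninformative.

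What is missing is control of differential change in the primary model, and nothing wider. The bias of 3.41 points and the rejection rates of 8.5% to 19.7% illustrate assumed confounding and do not predict what this study will show. The conclusion rests on reading the listed covariates as main effects. If covariate × time terms are already intended, the text needs only to say so.

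**What to change.** In 6.3:

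- Add motivation × time, with time categorical, to the primary model. Add at most a few other prespecified covariate × time terms, for example the stratification factors city and, for outcomes other than employment, baseline employment. Keep them few: there are 10 controls, and motivation, city and baseline employment together already use 8 parameters.
- Run the robustness check with and without the motivation × time terms.
- Reword the false-positive and attribution sentences to say that only the interaction terms and IPTW adjust the primary estimand, and only for the measured covariates. Economic need, exam scores and interview scores also guide selection and are not in the adjustment set.

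The cost is wording and a few model terms. If the covariates do not predict change, precision falls slightly: with the full set of terms the simulated SE rose from 0.344 to 0.365 SD (0.365/0.344 = 1.06, about 6%).
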